#### Study Incentives

For participants traveling to our office for in-person visits, we offered a US $10 incentive to aid with the cost of transportation and a monthly US $5 incentive to aid with cell phone and data costs. Participants were also compensated for their time at evaluation time points, receiving US $25 for completing their second visit and US $50 for completing the 6-month assessment visit. In addition, participants received US $10 for returning their accelerometer at visit 2 and at the 6-month visit. Each time the participants completed a monthly web-based questionnaire, they also received a US $10 incentive. Local participants received a voucher for a free 6-month gym membership worth US $60, and distance participants received US $60 toward the cost of a gym membership. Those in the PA intervention arm received the gym membership at the start of the study, whereas those in the control arm received the membership (or financial equivalent) at the 6-month follow-up.

#### 6-Month Visit

At the end of the 6-month intervention, participants were contacted again to set up their final assessment visit. Participants were mailed an ActiGraph accelerometer and asked to wear it for 7 complete days, following the baseline protocol. Participants were scheduled for their assessment visit on day 8 after they started wearing their monitor. *Distance participants* mailed the device back to our office on day 8 and conducted the visit with the study staff by phone.

At the start of the visit, the study staff reviewed the ActiGraph wear data to ensure that it was worn for sufficient time. Any participant with insufficient wear time was asked to rewear the accelerometer, and the visit was rescheduled. Participants then completed the same survey measures from the baseline assessment, with some additional process evaluation questions. Height, weight, and waist circumference were recorded again, followed by a 10-min treadmill walk (for in-person participants) and the PAR assessment. Finally, after the 6-month visit, the study staff conducted brief semistructured qualitative interviews with study participants who agreed to complete this interview.

### Measures and Outcomes

#### Demographics

Demographic questions at baseline assessed age, education, race, ethnicity, income, employment status, marital status, household size, country of birth, Hispanic subgroup, and years lived in the United States. In addition,, the Brief Acculturation Scale [65] asked 4 questions about languages used in different contexts.

#### PA Outcomes

The primary outcome measure is total PA, as measured by an accelerometer (ActiGraph wGT3X-BT). All participants were asked to wear an accelerometer for 7 days to measure their movement and intensity of activity. The minimum acceptable wear time is 5 days, with at least 600 min daily, or 4 days, with at least 3000 min total. The daily and weekly minutes of MVPA were calculated with Actilife software, using a minimum cutoff point of 1952 [66] to define the moderate-intensity PA and a minimum activity bout of 10 min, as current recommendations suggest that MVPA activities should last at least 10 min at a time [67,68]. Accelerometers have been validated with both total energy expenditure [69] and heart rate telemetry [70].

A self-reported measure of total weekly PA was also included as an outcome measure of MVPA. Using the 7-day PAR [62,63], an interviewer asked participants about moderate, hard, and very hard activities that they might have engaged in during each morning, afternoon, and evening over the past week. The 7-day PAR has repeatedly shown acceptable internal consistency, reliability, and concurrent validity with objective measures of PA [71-75], along with sensitivity to changes [72,73] in both moderate and intensive levels of PA [74,75]. In addition, the 7-day PAR demonstrated test-retest reliability among Latino participants [76]. The 7-day PAR data were assessed to overlap with accelerometer wear to corroborate the self-reported data.

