Other website features included resources to promote PA. Participants could access city guides containing useful information on where to be active in their city (eg, parks, bike paths, gyms, and local recreation centers), a list of free PA promotion apps participants could download on their smartphones, a series of Spanish language exercise videos found on YouTube, and concise daily and weekly tips published on the website throughout the 6-month intervention as well as detailed 2- to 3-page *tip sheets*. In the first 2 months, all participants received the following tip sheets: how to set achievable goals for PA, finding the time for PA, how to fit in short sets of PA throughout the day, and motivating yourself to be more physically active. Then, during their first monthly survey on the website, participants chose to receive up to 15 tip sheets of interest selected from a list of 20. Those tip sheets were then published on their website account throughout the intervention on a weekly or biweekly basis. Sample topics that participants could choose to receive included stretching, being active as a family, tips to exercise correctly, exercising outside, rewarding yourself for achieving your PA goals, etc. In addition, the website contained a community forum (for participants to write messages and interact with each other), an *Ask the Expert* area (where participants could ask a question and study staff post responses), and a section where participants could alert the staff if they sustained an injury during the study. Participants were also given a pedometer to help track their daily steps; alternatively, participants could choose to log daily steps using an app on their smartphone. See Multimedia Appendix 1 for screenshots of the website.

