At the end of the visit, the staff members reviewed the study goals and expectations and asked the participants to do the following:

Try to do MVPA for at least 10 min at a time, with no breaks.Track how much exercise they perform each day and log the time on the website.Wear the pedometer every day and log the steps on the website.Review and revise the exercise goal each week to work up to 150 min of MVPA each week by the end of 6 months in the study.Complete the monthly questionnaire on the website.

*Distance participants* completed visit 2 by phone and were guided through the same steps by the study staff. The visit was broken into 2 parts. Part 1 was completed on the day immediately after 7 consecutive days of accelerometer wearing. A staff member gave the participant a detailed explanation of what MVPA feels like, including examples of activities at this level. The staff member then completed the PAR by phone. The participant was instructed to return the accelerometer by mail, with a preaddressed envelope. Once the device was received back at the office, the study staff reviewed the data to ensure sufficient wear time and then scheduled part 2 of the visit by phone. In part 2, the *distance participant* was randomized into one of the study arms using the same randomization procedure as local participants, and then, the staff member guided the participant through the website and other study components by phone.

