#### Planned Analyses

The primary aim of this study is to determine the feasibility, acceptability, and preliminary efficacy of the tailored PA intervention. We will consider the intervention feasible if at least 80% of the randomized participants are retained at the 6-month follow-up. The intervention will be considered acceptable if at least 80% of participants completing the 6-month follow-up respond favorably (*satisfied* or *very satisfied*) to the question *In general how satisfied were you with the intervention?* on the 6-month follow-up survey. We also asked more questions about intervention and study acceptability on the 6-month survey and the poststudy qualitative interviews described earlier. The main efficacy outcome was minutes per week of total MVPA, as measured by accelerometer data and PAR self-report, assessed at baseline and 6 months after baseline. The hypothesis is that participants in the PA intervention condition will have greater increases in minutes of total MVPA from baseline to post intervention (6 months) than participants in the control condition.

As a preliminary step, we will assess potential between-group differences in baseline characteristics (demographics and baseline PA level) using graphical methods and nonparametric and parametric tests as appropriate (eg, the Wilcoxon rank sum test for skewed data, *t* tests for normally distributed continuous data, and chi-square tests for categorical data). Any variables not balanced by randomization will be controlled for as covariates in subsequent analyses if they are correlated with the outcome (eg, minutes per week of MVPA) at a modest *P*<.10 level. We will estimate the preliminary efficacy of intervention compared with control using a generalized linear model in which we regress minutes per week of objectively measured MVPA at 6 months on the treatment assigned, baseline value of the outcome, and potential confounders (including those variables not balanced by randomization). To avoid the effects of outliers, we apply a normalizing transformation (if necessary) to the outcome before analysis. Should this transformation not adequately bring the data toward normality, we will model the median outcome (instead of the mean) using a quantile regression model.

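### The accelerometer outcome named total MVPA counts only bouts of 10 minutes or more, and bout advice appears to go to the PA arm alone, so the score cannot separate more activity from regrouped activity

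*Protocol article*

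**What the plan says.** Under PA Outcomes the article states: "The primary outcome measure is total PA, as measured by an accelerometer (ActiGraph wGT3X-BT". The same paragraph gives the scoring rule: a cut point of 1952 for moderate intensity and "a minimum activity bout of 10 min". The reason given is "as current recommendations suggest that MVPA activities should last at least 10 min at a time".

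Planned Analyses uses the broader label: "The main efficacy outcome was minutes per week of total MVPA, as measured by accelerometer data and PAR self-report". The hypothesis there is that the PA arm "will have greater increases in minutes of total MVPA from baseline" than controls. The Abstract also says total MVPA. None of these statements repeats the bout limit.

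Visit 2 describes setting up the PA arm's website account, a personal exercise goal and a first-week activity plan. The requests that close this account include "Try to do MVPA for at least 10 min at a time, with no breaks", along with wearing the pedometer and logging exercise. The control-group section describes nutrition and wellness content unrelated to PA, and mentions no advice on bouts.

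**The concern.** The hypothesis is about an increase in total MVPA, but the score sees only the part that falls in longer spells. If only the PA arm is advised to be active in such spells, that part can grow in two ways: men do more, or they do the same amount in longer runs. Only the first supports the hypothesis as worded. Randomization does not remove the ambiguity, because the advice is part of the assigned treatment.

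This matters even in a pilot. Planned Analyses says the goal is to estimate effect sizes, and Power Analysis says they will be used to size a future RCT. An estimate labelled total MVPA that contains some regrouping would carry the wrong quantity into that trial.

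**Working it through.** **1. Label against score.** The label is total PA or total MVPA (Abstract, PA Outcomes, Planned Analyses). The score is minutes at or above the 1952 cut point in bouts of at least 10 min (PA Outcomes). No accelerometer outcome counting all MVPA minutes is described. The article can state the limit when it wishes: the Visit 2 eligibility check ties the 60-minute ceiling to bouts of 10 min or more, while the inclusion criteria give the same ceiling without bouts.

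**2. Who receives the bout advice.** The closing list in Visit 2 refers simply to the participants. Its other items (exercise goal, pedometer, activity log) fit only the PA arm, and it follows directly on that arm's set-up. The 10-minute treadmill walk reaches in-person men in both arms before randomization, but its stated purpose is more accurate self-report.

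**3. The plan's own figures (Power Analysis).** Inputs: mean change 42.5 (SD 81.8) versus 9.0 (SD 45.7) min/week; 25 per arm; two-sided alpha .05.

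- Difference: 42.5 − 9.0 = 33.5 min/week.
- SD: √[(81.8² + 45.7²)/2] = √4389.9 ≈ 66.3 min/week.
- d = 33.5/66.3 ≈ 0.51, as stated.
- Power by normal approximation, Φ(d√(25/2) − 1.96): 43.8% at d = 0.51 and 75.5% at d = 0.75. By noncentral t: 42.4% and 73.8%. The stated 43% and 75% reproduce, so the power figures are not in question.

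**4. What regrouping could do.** Suppose PA-arm men move on average x min/week from shorter spells into bouts of at least 10 min, controls do not, and all-minute MVPA is unchanged in both arms. Apparent d = x/66.3:

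| Assumed x (min/week) | Apparent d, bouted score | d, all minutes counted |
|---|---|---|
| 10 | 0.15 | 0 |
| 20 | 0.30 | 0 |
| 33.5 | 0.51 | 0 |

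Partial regrouping inflates the estimate without creating all of it. For example, if 10 of an observed 33.5 bouted minutes were regrouped and the rest were new, the all-minute gain would be 33.5 − 10 = 23.5 min/week.

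Every x is an assumption. The SD is borrowed from the planning study, and the article does not say whether that study's minutes were bouted. The planned model also adjusts for baseline, so these d values are approximate.

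**The case against.** The strongest reply is that this is a design choice, openly made. The bout rule is stated with its reason, the Visit 2 eligibility check uses bouts too, and the target behaviour is activity in such bouts. Total plausibly means summed over leisure, lifestyle, transportation and occupational activity, a contrast the Website section draws itself. The intervention content promotes added activity, and nothing tells men to consolidate existing minutes. The trial is a pilot that does not expect significance.

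Most of this stands, and it is why the bouted outcome should remain primary. It does not close the gap. An all-domains reading still does not make the score a count of all MVPA minutes, and a recommendation on bout length justifies measuring bouted MVPA but not inferring a rise in total MVPA from it alone. The 7-day PAR does not settle the matter: it is self-report, and no bout rule is stated for it as an outcome. Nor is this only a detail left to a fuller document, because the article itself fixes both the label and the score.

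Three stronger readings are tempting but unsupported:

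- A reader might infer that a positive result would be an artefact. The article gives no sign that regrouping occurs and no share of MVPA in short spells.
- A reader might take the tip sheet on "how to fit in short sets of PA throughout the day" as advice the score ignores. Set length is not given, and a sample text message suggests 15-minute walks, which would count if unbroken and intense enough.
- A reader might expect many zeros to undermine the mean model. The plan already provides a normalizing transformation and then median regression; whether these suffice is a separate question.

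**Conclusion.** The point holds in a limited form. The rule is neither hidden nor wrong. The fault is that the label and hypothesis are broader than the score, while the score matches advice that, read from context, goes to one arm. The bouted estimate alone therefore cannot support a statement about total MVPA, or supply an unambiguous total-MVPA effect size for the next trial.

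The size of any distortion is unknown. The range of d from 0.15 to 0.51 shows what assumed regrouping of 10 to 33.5 min/week would produce under the planning SD; it is not a forecast. In particular, the match at 33.5 min/week follows from choosing the planning difference as the input, and is no evidence that regrouping would explain the planned effect.

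**What to change.** Keep the bouted outcome as primary and call it *MVPA in bouts of at least 10 min* wherever the accelerometer outcome is now called total: the Abstract, PA Outcomes and Planned Analyses, including the moderator models.

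Re-score the same accelerometer files at the 1952 cut point with no bout minimum. Report that all-minute MVPA as a named supportive outcome, using the same model as the primary. Describe the effect as an increase in total MVPA, or carry it forward as such to size the future RCT, only if the all-minute estimate agrees. What counts as agreement should be written down before the arms are compared on it.

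The cost is one re-scoring run, one extra model and one more estimate to report. No new data are needed, and the article describes cleaning and analysis as still under way.

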#### Psychosocial Variables

Readiness to change, self-efficacy, and processes of change were also assessed as psychosocial constructs related to PA. The 5-item PA stages of change questionnaire determines whether a participant is in the precontemplation, contemplation, preparation, action, or maintenance stage of PA change. This measure has demonstrated reliability and concurrent validity with measures of self-efficacy and current activity levels [77,78]. The 40-item processes of PA change measure asks participants how often (never, seldom, occasionally, often, or repeatedly) they engage in various cognitive and behavioral strategies associated with behavior change [79]. The measure contains 5 behavioral subscales (counterconditioning, helping relationships, reinforcement management, self-liberation, and stimulus control) and 5 cognitive subscales (consciousness raising, dramatic relief, environmental re-evaluation, self–re-evaluation, and social liberation). A 5-item self-efficacy measure was included to assess confidence in one’s ability to exercise in various situations on a 5-point scale, ranging from not at all confident to extremely confident [77]. In addition to being administered at baseline and at 6-month follow-up, the readiness to change, self-efficacy, and processes of change measures were administered on a monthly basis via the website to help generate the computer-based, expert system feedback reports for the intervention group.

Additional psychosocial measures related to PA included social support, PA enjoyment, perceived stress, and perceived quality of life. The social support measure (social support for exercise) [80] included 2 sets of 14 items (1 set for friends and 1 set for family) related to the frequency with which friends or family members provided social support for PA over the past 3 months, with response options including none, rarely, a few times, often, very often, or does not apply. The Physical Activity Enjoyment Scale [81] measures the level of enjoyment that a person derives from engaging in PA. Using a scale of 1 to 7, participants were asked to rate their feelings on 18 items about their enjoyment of PA (eg, a rating of 1 means *I find it pleasurable* and a rating of 7 means *I find it unpleasurable*). The Perceived Stress Scale [82,83] is a widely used, validated instrument composed of 10 items to measure perceived stress in the past month, with a 5-point scale, where 0 means never and 4 means very often. The perceived quality of life was measured using a single item modified from the 26-item World Health Organization Quality of Life measure [84]. Participants were asked to rate their quality of life as excellent, very good, good, or poor.

#### Neighborhood Measures

Measures of neighborhood safety, neighborhood social cohesion, neighborhood police attitudes, and fear of police were also administered. Neighborhood safety was assessed with a single item [85] asking participants if they felt safe in their neighborhood all of the time, most of the time, some of the time, or none of the time. The Neighborhood Social Cohesion [86] scale is a reliable, validated set of 4 items asking participants to rate their level of agreement with statements about their neighborhood. Neighborhood police attitudes were assessed with 7 items asking whether police activities in the neighborhood (eg, stopping too many people on the street without a good reason, stopping people because of the color of their skin, being rude to people they stop, and disrespecting women when they stop them) were a big problem, some problem, or no problem [87,88]. Fear of police was assessed with 2 questions that asked if the participant agrees or disagrees (strongly agree, agree, neither agree nor disagree, disagree, and strongly disagree) with the following statements [87]: Are you sometimes afraid that police will stop you and threaten to arrest you when you are completely innocent? and Are you sometimes afraid that police will stop and threaten to arrest one of your children, or a younger member of your family, when they are completely innocent? On the basis of our earlier work [89], a new neighborhood police attitude question developed by our team was included to ask how worried a participant was that police would stop them if they were exercising in their neighborhood. Response options to this question included not at all worried, somewhat worried, and very worried.

#### Built Environment Measures

To assess built environment factors that influence PA, including land use characteristics, sidewalks, shoulders and bike lanes, street characteristics, and quality of the pedestrian environment, we used Objective Neighborhood Audits using Google Street View [90-92] and the Active Neighborhood Checklist (ANC) [93]. We used a 0.5-mile buffer around participants’ homes. We used Google Street View to conduct the ANC audit, which has demonstrated excellent reliability with in-person audits and audits comparing new, archived, and commercial imagery [91,94].

#### Control Group Measures

For the nutrition and wellness control arm, a wellness questionnaire assessed knowledge regarding the men’s wellness topics presented in the control materials. We also assessed pre and post fruit and vegetable intake using the National Cancer Institute's *Eating at America's Table All Day Screener* [95].

#### Process Evaluation

Standardized protocols were used in training staff to conduct all study visits. All PAR questionnaires were reviewed for errors before data entry. To ensure receipt of treatment, phone calls were conducted 1 week and 1 month post randomization to ensure proper use of the pedometer and self-monitoring on the website. Participants who were not completing their PA logs or their monthly web-based questionnaires were also contacted. To measure fidelity and dose of treatment implementation—and to provide insight into participant usage—the website captured the number of log-ins and views of each page or link; how much time participants spent on the website; and what participants entered on the website, that is, goals, discussion board posts, *Ask the Expert* submissions, etc; data were tracked by user selections and time stamped accordingly. Receipt of text messages was assessed by the text messaging system, and Facebook participation was measured by counting participants’ engagement such as likes, comments, and posts.

#### Feasibility

Our main feasibility measure is a participant retention rate of 80% or more. To inform a future study, we also measured time to recruit 50 participants, what proportion of recruited participants were eligible and reasons for ineligibility, the yield of various recruitment methods, and baseline process data (proportion of eligible participants who completed study visits, length of visits, time range from initial recruitment to randomization, visits attempted and completed on different days, duration of visit, refusals, and interviewer notes on surveys). Six-month visit process data included duration of the visit, the proportion of randomized participants completing the study, and those who refused or were dropped from the study along with reasons for dropping as well as participants we were unable to reach for follow-up.

